### Outcomes {12}

The primary outcome of interest is HbA1c, a clinical measure of diabetes management. We will measure the change in HbA1c from baseline (must be from within the 90 days prior to enrollment) to the 12-month study end point. HbA1c will be measured every 6 months, with the first 6-month measurement serving as our tailoring variable for the SMART. Patients with an HbA1c reduction of at least one percentage point will be considered responders [29].

The secondary outcomes of interest are implementation outcomes and patient-centeredness. The implementation outcomes that will be measured include appropriateness, fidelity, sustainability, and patient-centeredness. We define appropriateness as the perceived fit or compatibility with the patient population, staff, and organization; fidelity as the degree to which the intervention is implemented as intended; and sustainability as the extent to which the treatment is sustained or maintained. Patient-centeredness will be measured using the six dimensions defined by the Institute of Medicine. See Table 2 for a full list of outcomes measures and data sources.

**Table 2 Tab2:** Outcomes and data sources

**Domain**	**Specific measurement**	**Specific metric**	**Method of aggregation**	**Timepoint**	**Data source**
Clinical Effectiveness	HbA1c	Change from baseline	Proportion of participants with a decrease of at least 1 percentage point	6 and 12 months post enrollment	EMR
Fidelity	Active RGM Usage	Value at intervention completion	Binary value (Y/N: at least one upload of data within a 30-day period and at least 16 blood glucose entries within a 30-day period)	6 months after enrollment or rerandomization^a^	Glooko Reports
	DSMT attendance	Value at intervention completion	Binary value (Y/N: attended at least three of four sessions)	6 months after enrollment or rerandomization^a^	DSMT Attendance Sheets
	Adherence to CHW engagement	Value at intervention completion	Binary value (Y/N: completed initial education session, SDoH screener, and at least three meetings with CHW)	6 months after enrollment or rerandomization^a^	CHW Log Sheet
Appropriateness	Perceived appropriateness, fit, and compatibility with patient population and organization from the perspectives of Center staff and patients	Qualitative self-reported experiences	N/A	Between 3 and 6 months after enrollment or rerandomization^a^	Center Staff Interviews Patient Focus Group Discussions

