### Sample size {14}

The sample size calculation, performed using G*Power (version 3.1), is based on the primary outcome of HbA1c over the 12-month study period, with the primary predictor being the six treatment conditions taken over the course of the study. The Null (H0) and Alternative (H1) Hypotheses are H0: There is no difference in the mean change in HbA1c among the six treatment groups, and H1: There is a significant difference in the mean change in HbA1c among the six treatment groups. The analysis assumes a significance level of 5%, 80% power, six treatment groups, equal group allocation, and a medium effect size of *f* = 0.25. The effect size of *f* = 0.25 was selected based on Cohen’s conventions for effect sizes in behavioral sciences, where 0.10 represents a small effect, 0.25 represents a medium effect, and 0.40 represents a large effect. A medium effect size is considered appropriate for this study, as it balances the detection of meaningful clinical differences with practical sample size considerations. Previous studies on diabetes management interventions such as DSMT and RGM have reported effect sizes in this range, indicating that a medium effect size is a reasonable expectation for interventions aimed at reducing HbA1c [13, 25].

The sample size estimation properly accounted for the multiple groups and comparisons inherent in the SMART design. Specifically, we conducted the sample size estimation for detecting a difference in HbA1c change across the six treatment groups, using an ANOVA framework, which inherently accounts for multiple comparisons. To ensure robustness and accommodate potential dropouts, we inflated the sample size by 20%. Thus, the minimum required sample size is 216 patients, and to account for an anticipated dropout rate, we aim to recruit 270 patients. This approach ensures that the study is adequately powered to detect significant differences across all treatment conditions, providing a solid basis for our subsequent analyses.

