## Data collection and management

### Plans for assessment and collection of outcomes {18a}

#### Intervention outcome measure

The primary outcome of our study is change in HbA1c which will be calculated as three measures. We will collect HbA1c at baseline (no more than 90 days prior to patient intake), 6-month follow-up, and 12-month study end point. First, we will use change in HbA1c as the tailoring variable for our SMART. We will calculate change in HbA1c from baseline intake to 6-month follow-up. Then we will calculate change in HbA1c from baseline to 12-month follow-up and from 6-month to 12-month follow-up. Because HbA1c is an average measure of blood sugar levels of the past 3 months, clinicians often order an HbA1c test every 90 days. If it has not been at least 90 days since the patient’s last HbA1c at the 6- or 12-month follow-up, we will use an HbA1c point of care test kit (HbA1c Now by Bayer) to measure the patient’s HbA1c.

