#### Primary outcomes

To optimize the adaptive intervention and understand the causal effects of each proposed sequence, we will employ a SMART design. This design is particularly advantageous for chronic diseases like diabetes, where there is significant heterogeneity in response to treatment. The SMART design allows for re-randomization based on a tailoring variable, which in our study is the change in HbA1c at 6 months, enabling patients to receive an adaptive intervention that is most suited to their needs. To address potential imbalances in randomization, we will use stratified and block randomization techniques.

For primary analysis, we will employ linear regression models adjusting for baseline characteristics utilizing type III sum of squares to account for these discrepancies. Sensitivity analyses will include inverse probability weighting to account for any imbalances. To assess the overall HbA1c reduction by treatment condition and the average patient percentage point reduction in HbA1c from baseline to 12 months within each of the six treatment conditions, we will utilize one-way ANOVA for mean comparisons, followed by pairwise comparisons with a Tukey post hoc test to correct for multiple comparisons. In cases of non-normal data distribution, we will opt for Kruskall-Wallis tests and a Dunn post hoc test with Hommel multiple comparison *p*-value corrections.

Linear regression will be employed to adjust for additional covariates that may confound the relationship between treatment and outcome, such as baseline characteristics with residual confounding post-randomization, and baseline and 6-month HbA1c values. We will also test for possible interactions of covariates with the treatment variable, reporting model adjusted slopes (β_ADJ_), 95% confidence intervals, model diagnostics, and goodness of fit (via R^2^).

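### A further regression under the primary outcomes adjusts the 12-month treatment comparison for 6-month HbA1c, which removes whatever the first stage achieved by month 6

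*Protocol article*

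**What the plan says.** The Primary outcomes part of Statistical methods {20a} describes several analyses of HbA1c change:

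- a linear regression, named as the primary analysis, that adjusts for baseline characteristics;
- a one-way ANOVA with Tukey comparisons of the "reduction in HbA1c from baseline to 12 months within each of the six treatment conditions";
- a further linear regression for covariates thought to confound treatment and outcome, including "baseline characteristics with residual confounding post-randomization, and baseline and 6-month HbA1c values", whose adjusted slopes and 95% confidence intervals are to be reported;
- Q-learning to find the best regime.

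The third item is the subject of this point. Nothing in its paragraph limits the 6-month covariate to comparisons made after re-randomisation.

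Other sections fix the role of that measurement. Intervention description {11a} places the DSMT/RGM randomisation at enrolment, after baseline data collection. Outcomes {12} describes HbA1c as measured every 6 months, "with the first 6-month measurement serving as our tailoring variable for the SMART". The section on the outcome measure in {18a} says: "We will calculate change in HbA1c from baseline intake to 6-month follow-up". Objectives {7} (Aim 3) and Trial design {8} (path E expected to do best) concern entire sequences of interventions.

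**The concern.** A confounder must precede the treatment whose effect is being estimated, or at least not result from it. For the first randomisation, 6-month HbA1c is a result: it is what six months of DSMT or RGM produced, and it lies on the route to the 12-month value. Holding it constant compares patients as if the first stage had brought them to the same point by month 6.

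The reported slope would then answer a question about months 6 to 12 while being presented as a 12-month treatment effect. The same section also contains a baseline-adjusted regression and an ANOVA, so the paper could show conflicting answers to what looks like one question. A reader of the adjusted slopes could conclude that it makes little difference whether DSMT or RGM comes first, when the model had taken that difference out.

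**Working it through.** **The plan's own figure.** Sample size {14} states: "The analysis assumes a significance level of 5%, 80% power, six treatment groups, equal group allocation, and a medium effect size of" f = 0.25. For a one-way ANOVA with six groups, the noncentrality is f² × N, with 5 and N − 6 degrees of freedom. Power first reaches 0.80 at N = 211 (0.8003). The next multiple of six is 216, where the noncentrality is 0.0625 × 216 = 13.5 and power is 0.811. With 20% dropout, 216 / 0.80 = 270. Both stated figures reproduce. They rest on the ANOVA, which does not contain 6-month HbA1c, so this point does not change them.

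**The structural result, which needs no assumed figure.** Write Y0, Y6 and Y12 for HbA1c at baseline, 6 and 12 months. Then

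Y12 − Y0 = (Y12 − Y6) + (Y6 − Y0).

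If Y0 and Y6 are both covariates, the second bracket is an exact linear combination of covariates. Moving it across the equation changes only the coefficients of Y0 and Y6 (by −1 and +1). Every treatment coefficient is the same whether the outcome is 0-12 or 6-12 month change. In simulated data the two sets of coefficients agreed to about 1e-14.

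**What is lost.** Suppose the first stage shifts Y6 by δ, a share c of the 6-month level carries to month 12, and the first stage has a further direct effect τ after month 6. Second-stage treatment aside, the first-stage effect at 12 months is cδ + τ. With Y6 in the model and no unmeasured cause shared by Y6 and Y12, the coefficient is τ alone.

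**Size under assumed inputs.** The documents give no SD, first-stage effect or carry-over. The following ranges are assumptions: δ 0.3 or 0.5 points; c 0.5, 0.8 or 1.0; τ 0 or 0.2 points; shared unmeasured cause absent or of size 0.5. Each scenario was a simulated SMART of 400,000 patients, analysed with and without 6-month HbA1c (baseline HbA1c always included). Selected results, in HbA1c points, negative favouring DSMT first:

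| δ | c | τ | Shared cause | DSMT − RGM, without → with Y6 | Removed | Path E − (RGM to CHW) in six-condition model, without → with Y6 |
|---|---|---|---|---|---|---|
| 0.5 | 0.8 | 0 | no | −0.332 → −0.001 | 100% | −0.160 → 0.001 |
| 0.5 | 0.8 | 0 | yes | −0.329 → +0.079 | 124% | −0.106 → +0.086 |
| 0.5 | 0.8 | 0.2 | no | −0.533 → −0.202 | 62% | −0.379 → −0.214 |
| 0.5 | 0.8 | 0.2 | yes | −0.530 → −0.127 | 76% | −0.318 → −0.125 |
| 0.3 | 0.5 | 0.2 | no | −0.306 → −0.195 | 36% | −0.258 → −0.190 |

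The share removed is 1 − (with / without); in the third row, 1 − 0.202/0.533 = 62%.

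Over all scenarios:

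- τ = 0.2: 36-81% of the first-stage contrast was removed.
- τ = 0, no shared cause: 98-106%, that is, all of it apart from simulation error.
- τ = 0, shared cause present: 116-144%, a reversed sign.

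**Where the covariate does no harm.** The comparison of CHW with switching among DSMT non-responders stayed at about −0.30 with or without 6-month HbA1c. There it precedes the randomisation being analysed.

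**Why deletion is not enough for the six paths.** Patients enter a responder path because their HbA1c fell by month 6. In a simulated SMART with no treatment effect at either stage (assumed baseline SD 1.5, carry-over 0.5-0.7, shared cause absent or 0.5), a six-path model with baseline covariates only made the responder paths look 0.8-1.7 points better than path E. With 6-month HbA1c included, those differences were within 0.01. The table shows the same problem from the other side: in its first row, the path contrast without the covariate is −0.160, about half the arm contrast of −0.332.

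**The case against.** The strongest reply concerns scope. The regression named as the primary analysis adjusts for baseline characteristics only, the trial is powered on the ANOVA, and neither uses 6-month HbA1c. The criticised sentence comes later and offers its covariates as examples. Q-learning and g-estimation are also planned, and both are meant for sequences with an intermediate covariate. This stands: a reader might infer that the trial's primary analysis as a whole is adjusted for a post-randomisation variable, and the document does not support that. The regression is still listed under the primary outcomes, and its slopes and intervals are promised.

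A second reply is that in the six-condition model 6-month HbA1c really does determine path membership and predicts the outcome, so calling it a confounder is not absurd. This also stands in part. For paths it is a time-varying confounder that is itself affected by earlier treatment, so neither including nor omitting it gives a causal path comparison. That limits the remedy; it does not justify the covariate for first-stage or regime effects.

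Third, a reader might infer a definite loss, for example 40-80%. That range comes from 0.5 × (1 − ρ) with ρ, the correlation of 6- and 12-month HbA1c given baseline, between 0.4 and 0.8, and with a 0.5-point effect fully retained at 12 months. None of these inputs is in the document. Nor is understatement guaranteed, since a shared unmeasured cause can reverse the sign.

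**Conclusion.** The point holds for the further adjusted regression. As written, that model treats a first-stage outcome and tailoring variable as a confounder, and its treatment slopes describe months 6 to 12 instead of the full 12 months. This part is algebra and rests on no assumed figure.

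The size is not derivable from the document. Under the stated assumptions the distortion runs from about a third of the first-stage contrast to all of it. The sign reversed in the scenarios with a shared unmeasured cause and no later direct effect. The first-listed primary regression, the ANOVA, the sample size of 216 evaluable and 270 recruited patients, and second-stage comparisons within a first-stage arm are not affected by this covariate.

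**What to change.** Replace the single list of covariates with a statement of which effect each regression estimates:

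1. **First-stage effect (DSMT versus RGM) and embedded regimes.** Leave out 6-month HbA1c. Adjust for baseline HbA1c, site and other pre-randomisation covariates. Weight regimes for the re-randomisation probability. With the 60 and 60 envelopes per box in Sequence generation {16a}, that probability is 60/120 = 1/2, so a re-randomised non-responder gets weight 2 and a responder weight 1.
2. **Second-stage effect.** Keep 6-month HbA1c as a covariate among re-randomised non-responders within a first-stage arm, and in the stage-2 Q-function.
3. **Six-path comparison.** Present it as descriptive, with or without 6-month HbA1c, and rest causal claims on items 1 and 2. Simply deleting the covariate from the six-path model would leave responder paths looking better even if no treatment works.

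The cost is a few sentences in the protocol or analysis plan, best settled before outcomes are analysed. No extra patients, visits or data are needed.

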To determine the optimal dynamic treatment regime (DTR) that maximizes the greatest benefit of percentage reduction in HbA1c at each randomization stage of the study, we will employ a Q-learning algorithm. This algorithm utilizes a Q-function *Q* (s_*i*_, *t*_*i*_) to measure the quality of assigning a treatment (*t*_*i*_) to a patient at a specific stage (*s*_*i*_), with higher reductions in HbA1c percentages yielding higher quality. Regression models will be used to estimate these Q-functions, taking into account the outcome, treatment types, and all other covariates of interest. We will assess model diagnostics and fit, and test interactions to retain significant results. With the Q-function known, the optimal DTR π^∗^(*s*_*i*_, *t*_*i*_) is determined by the treatment (*t*_*i*_) which maximizes *Q* (*s*_*i*_, *t*_*i*_) given the stage (*s*_*i*_).

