## Discussion

Diabetes affects millions of Americans each year, including a disproportionate number of racial and ethnic minorities. It is increasingly expensive to our healthcare system and to individuals, and can have severe long-term health implications. Team-based care, and specifically interventions like diabetes education, leveraging technology like RGM, and integrating non-clinical staff like CHWs, have shown promise in improving health outcomes among certain populations [40, 41]. Yet there are still gaps in our understanding of how appropriate these interventions are for the population of interest, the degree to which we can maintain fidelity, and ultimately the potential change in HbA1c among specific populations. Specifically, various social determinants of health needs, which are linked to health outcomes, may not be addressed in the traditional patient-provider relationship. The intervention components of this study provide support towards better diabetes management will also addressing SDoH needs. Findings from this study will provide a nuanced perspective of the combination and sequence of interventions that best address the needs of specific patients.

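### The Q-learning step declares the maximiser of an estimated Q-function to be the optimal regime, with no sampling uncertainty attached to that declaration

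*Protocol article*

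**What the plan says.** The Q-learning paragraph (Protocol article, Statistical methods {20a}, Primary outcomes) opens with its purpose: "To determine the optimal dynamic treatment regime (DTR) that maximizes the greatest benefit of percentage reduction in HbA1c at each randomization stage of the study". It goes on: "Regression models will be used to estimate these Q-functions". The decision then begins "With the Q-function known, the optimal DTR" and ends with the treatment that maximises Q at that stage. The only filter in the paragraph is this: "We will assess model diagnostics and fit, and test interactions to retain significant results".

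Earlier in the same section are a linear regression with 95% confidence intervals and a one-way ANOVA over the six treatment conditions with Tukey comparisons. Neither is mentioned in the rule for the optimal regime. Section {20c} adds multiple imputation, Rubin's rules and g-estimation, but no criterion for naming a regime. The Sample size section {14} covers the six-group ANOVA only. The Discussion states the aim of the work: "Findings from this study will provide a nuanced perspective of the combination and sequence of interventions that best address the needs of specific patients".

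**The concern.** Within one paragraph an estimated function becomes a known one, and its sampling error drops out of the conclusion. Fitted values on a continuous scale are never exactly tied, so a maximum always exists. The rule has no margin, no bound and no wording for the case where the leading regime cannot be told from the rest.

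What is at stake is how the result is described. Identifying the best sequence is the gap that the article says the trial will fill, and the Trial design section states a favoured path in advance, DSMT then CHW. If nothing differs, the rule would still name the regime containing that path as optimal about one time in four. Without a statement of uncertainty this would read as confirmation.

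**Working it through.** **1. The plan's own figure.** The inputs in section {14} are: "The analysis assumes a significance level of 5%, 80% power, six treatment groups, equal group allocation, and a medium effect size of" 0.25. For a one-way ANOVA with noncentrality N·f², the smallest N for 80% power is 211. Six equal groups need 216 (36 each, power 0.811), and 216/0.8 = 270. Both stated numbers reproduce. They describe the omnibus test; no operating characteristic is given for choosing a regime.

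**2. Regimes being compared.** Section {16a} gives two second-stage options per first-stage arm: CHW or RGM after DSMT, and DSMT or CHW + RGM after RGM. Responders stay where they are. That makes four embedded regimes.

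**3. Information per second-stage cell.** Non-responders per cell = N × (1 − responder rate)/4. The documents give no responder rate; 20 to 50% is assumed.

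| N | 20% responders | 50% responders |
|---|---|---|
| 216 | 216 × 0.8/4 = 43 | 216 × 0.5/4 = 27 |
| 270 | 270 × 0.8/4 = 54 | 270 × 0.5/4 = 34 |

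**4. Gap that arises by chance.** Assume an SD of HbA1c change of 1.2 to 1.8 points and a correlation of 0.7 between 6- and 12-month change. After adjustment for 6-month change the residual SD is σ = SD × √(1 − 0.7²) = 0.714 × SD, that is 0.857 to 1.285. With m patients per cell, the standard error of the contrast is σ√(2/m), and with no true difference the mean absolute gap is √(2/π) × σ√(2/m).

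- Best case (SD 1.2, m = 54): standard error 0.857 × 0.192 = 0.165; mean gap 0.798 × 0.165 = 0.13 points.
- Worst case (SD 1.8, m = 27): standard error 1.285 × 0.272 = 0.350; mean gap 0.798 × 0.350 = 0.28 points.

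A true 0.3-point difference between the two options is therefore 0.3/0.350 = 0.9 to 0.3/0.165 = 1.8 standard errors.

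**5. Which regime is named.** Two-stage backward Q-learning was simulated under these assumptions: a regression among non-responders in each first-stage arm, then a first-stage comparison of the resulting pseudo-outcomes.

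| True advantage among non-responders of one path | Result |
|---|---|
| None | A regime is named every time; each of the four about 25% of the time |
| 0.3 points | Wrong regime named in about 16 to 48% of trials |
| 0.5 points | Wrong regime named in about 2 to 28% of trials |

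The ends of the ranges carry a few percentage points of simulation error. With no effect and an SD of 1.5, the best-looking regime appeared better than the worst by 0.28 to 0.36 points on average.

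**The case against.** The strongest reply is that this is textbook Q-learning: estimate Q, then take the maximiser. That stands. The maximiser is the usual point estimator, the word known is loose in a paragraph that has just said estimate, and choosing any of several truly equal regimes loses no HbA1c. The fault lies in what is attached to the choice, not in the choice itself.

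A reader might infer that the trial has a 100% type I error. The documents do not support that. The stated hypothesis test is the ANOVA at 5%; always returning a maximum is a property of a point estimator, not an error rate of that test. A reader might also infer that the trial cannot report that sequences were not distinguished. It can: the Tukey pairs include the two re-randomised options within each first-stage arm, and the regression reports intervals. But no text makes the naming of the optimal regime depend on either.

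Two further replies are weaker. Retaining significant results applies to interactions, not to the treatment contrast that decides the regime. Stretched to every treatment term at an unadjusted 5%, it would still leave a regime falsely declared in about 14% of trials with no effect. Rubin's rules are invoked for uncertainty from missing data, and section {20c} does not say how a pooled result would qualify the named regime. An analysis plan that is not shown may supply intervals, but the protocol sentence itself fixes how the optimal regime is determined.

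**Conclusion.** The point holds as one about an unqualified declaration. The rule calls the maximiser of an estimate optimal and attaches no sampling uncertainty. That a regime is named even when all are equal follows from the rule and needs no assumption. The sizes do rest on assumptions: the SD, correlation and responder rate are not in the documents, and the wrong-regime figures depend strongly on them. Across the assumed range the trial has limited information for separating regimes that differ by 0.3 points. At 0.5 points the picture runs from comfortable to poor. The finding does not show that Q-learning is the wrong method or that the trial's formal test is invalid.

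**What to change.** Change the paragraph as follows:

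- Replace known by estimated, and keep the maximiser as the estimated best regime.
- Report the four embedded regime means and the stage contrasts with simultaneous (multiple-comparisons-with-the-best) confidence bounds that are valid for Q-learning.
- List the regimes not distinguishable from the best.
- Describe a regime as shown to be optimal only when all the others are excluded. Otherwise describe it as the estimated best among regimes not distinguished, without claiming that they are equivalent.

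This costs a paragraph and some code, and no new data. The real downside is that a single regime will seldom be shown to be optimal at this sample size. In one assumed scenario (N = 216, SD of change about 1.56, about 37% responders), a conservative Bonferroni form without covariate adjustment left a single regime in 0.2% of trials with no effect, 4.8% at a true 0.5 points and 23.7% at 0.8. The maximiser was the right regime in 82.2% and 96.5% of trials at those two advantages. That is why the maximiser should still be reported as the estimate.
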